**Major injuries**
Bladder or ureteral injury requiring intervention
Bowel injuries requiring intervention
Diaphragmatic injuries requiring intervention
Gynecological injuries requiring intervention
Hepatobiliary injuries requiring intervention
Hip fractures requiring intervention
Male genital injuries requiring intervention
Pancreatic injuries requiring intervention
Pelvic fractures (major—excludes minor avulsion injuries and non-displaced ring fractures) requiring intervention
Pelvic fractures (minor) requiring intervention
Renal injury requiring intervention
Retroperitoneal injuries requiring intervention
Spinal injuries (unstable or with neurological compromise) needing observation or intervention
Spinal injuries (stable with no neurological compromise) requiring intervention
Splenic injury requiring intervention
Vascular injury (aortic) needing observation or intervention
Vascular injury (pelvic vessels) requiring intervention
Vascular injuries (other vessels) requiring intervention
**Minor injuries**
Bladder or ureteral injuries needing observation, but not requiring intervention
Bowel injuries needing observation, but not requiring intervention
Diaphragmatic injuries not requiring intervention (observation status is irrelevant)
Gynecological injuries needing observation, but not requiring intervention
Hepatobiliary injuries needing observation, but not requiring intervention
Hip fractures needing observation, but not requiring intervention
Male genital injuries needing observation, but not requiring intervention
Pancreatic injuries needing observation, but not requiring intervention
Pelvic fractures (major—excludes minor avulsion injuries and non-displaced ring fractures) not requiring intervention (observation status is irrelevant)
Pelvic fractures (minor) needing observation, but not requiring intervention
Renal injury needing observation, but not requiring intervention
Retroperitoneal injuries needing observation, but not requiring intervention
Spinal injuries (stable with no neurological compromise) needing observation, but not requiring intervention
Splenic injury needing observation, but not requiring intervention
Vascular injury (aortic) that do not need intervention or observation
Vascular injury (pelvic vessels) needing observation, but not requiring intervention
Vascular injuries (other vessels) needing observation, but not requiring intervention

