## Materials and methods

### Defining primary outcomes via expert panel review

Previous experience has shown that clinicians differ in their tolerance for missing minor injuries and in their definitions as to what constitutes a clinically significant injury. Many clinicians are comfortable using tools that occasionally miss injuries that require no intervention, provided all major injuries are identified. Other clinicians seek to identify all injuries regardless of their clinical significance [38].

To accommodate varied perspectives on clinically significant injury, we employed a modified Delphi process and convened an expert panel consisting of three trauma surgeons, three emergency medicine physicians and radiologist to define the following study outcome classifications of injuries seen on CT: clinically significant major injury, minor injury, and insignificant injury.

Our final outcome classification scheme is based in results of this Delphi process among this expert panel. Under this schema, injuries of major clinical significance consist of all abdominal and pelvic injuries requiring intervention, as well as any injury to the aorta, and any injury to the spine associated with instability or neurological compromise. Injuries that require only observation, but no intervention, will be considered clinically minor, provided they do not involve the aorta or spine, while injuries that required neither intervention nor observation will be considered insignificant. See Table 1.

**Table 1 pone.0271070.t001:** Classification of injuries based on Delphi consensus.

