We will assign a final clinical outcome for each patient based on the results of A/P CT imaging as well as the patient’s hospital course. Patients who we designate as having injuries must have injuries evident on CT imaging. This reflects the fact that if injuries are not apparent on CT imaging, it is immaterial whether the patient underwent such imaging. Furthermore, we will classify each patient as having, in order of increasing severity: 1—no injuries (no injuries evident on CT); 2—insignificant injuries (e.g., minor bruising, small hematomas, or isolated small avulsion fractures); 3—clinically minor injuries (significant injuries that require no specific intervention); and 4—clinically major injuries (significant injuries that require specific intervention or result in patient death). Our final outcome classification will be based on the most severe type of injury sustained by each patient. We will concatenate our final outcome assignments with the criterion assessments to create our final analysis database.

We will apply chi-squared binary recursive partitioning to this data set to identify separate combinations of criteria that identify both major and minor significant abdominopelvic injuries with > 98% sensitivity and > 98% NPV, assuming such combinations exist. If more than one combination of variables exhibits the requisite sensitivity and negative predictive values for injury, the combination with the highest specificity will be adopted as the optimal low-risk decision instruments.

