**Renal Injury**				
**Retroperitoneal Injuries**				
**Spinal Injuries–Unstable or with neurological compromise**				
**Spinal Injuries–Stable and with no neurological compromise**				
**Splenic Injuries**				
**Vascular Injuries–Aorta**				
**Vascular Injuries–Pelvic Vessels**				
**Vascular Injuries–Other Vascular Injuries**				

^a^Classification—Injury categories

No injury = No injury evident on A/P CT imaging

Clinically Insignificant injury = Unimportant injury that could be missed without significant consequences

Clinically Minor = Injury that may not require therapy, but is important to diagnose

Clinically Major = Injury that is associated with diagnostic and therapeutic implications

^b^Excludes minor avulsion injuries and non-displaced anterior ring fractures

^c^Minor fractures and non-displaced anterior pelvic ring fractures

**Interventions include:** Surgical intervention; Fracture reduction, repair or stabilization; Interventional radiology procedures or embolizations; Administration of blood or blood products; Reversal of anticoagulation; Administration of pressors

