#### Conclusions

Injuries of major clinical significance consist of all abdominal and pelvic injuries requiring intervention, as well as any injury to the aorta, and any injury to the spine associated with instability or neurological compromise. Injuries that require only observation, but no intervention, were considered clinically minor, provided they did not involve the aorta or spine, while injuries that required neither intervention nor observation were considered insignificant.

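### The primary outcome, major injury, is defined inconsistently for aortic and unstable-spine injuries managed without intervention

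*Protocol article*

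**What the plan says.** The rule for major injury appears in four forms in the protocol article.

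- **General rule.** Under Defining primary outcomes via expert panel review, "injuries of major clinical significance consist of all abdominal and pelvic injuries requiring intervention, as well as any injury to the aorta". Unstable or neurologically compromised spine injuries are added on the same terms. Injuries that are only observed "will be considered clinically minor, provided they do not involve the aorta or spine". The section then points to Table 1 as the scheme. The Conclusions under Defining significant injuries of the abdomen and pelvis repeat the rule, with minor status for observed injuries "provided they did not involve the aorta or spine, while injuries that required neither intervention nor observation were considered insignificant".
- **Table 1.** Aortic and unstable-spine injuries are major when they need observation or intervention. The minor list contains "Vascular injury (aortic) that do not need intervention or observation". No list has a row for an unstable-spine injury needing neither. The minor list also contains "Diaphragmatic injuries not requiring intervention (observation status is irrelevant", and treats major pelvic fractures the same way.
- **Phase 1 outcome scale.** The top level is "clinically major injuries (significant injuries that require specific intervention or result in patient death". The level below takes significant injuries without a specific intervention. Neither level makes an exception for the aorta or the spine.
- **Table 2 form.** Footnote a reads "Clinically Major = Injury that is associated with diagnostic and therapeutic implications". The form also lists what counts as an intervention, but it does not refer to Table 1.

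Outcome ascertainment adds that a death caused by the injury counts when judging the need for intervention, and that classification rests on procedural records.

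**The concern.** Major injury is the reference standard for the primary instrument. It is the outcome of the first recursive partitioning, the basis of the sensitivity sample size, and the condition that makes a rule-negative patient a false negative. If two statements class the same patient differently, the derivation target, the sensitivity denominator and the count of missed injuries depend on which statement the coder follows. A definition left open until data are in can also be settled after the results are known.

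The disputed patients are those managed without a procedure. Procedural records, the stated source for classification, would not by themselves identify them.

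**Working it through.** **Step 1: the definitions side by side.** In this table, neither means that neither intervention nor observation is needed.

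| Injury | General rule (Methods text, Delphi Conclusions) | Table 1 | Phase 1 scale |
|---|---|---|---|
| Aorta, neither | Major | Minor | Not major unless the patient dies |
| Aorta, observed only | Major | Major | Minor unless the patient dies |
| Unstable spine, observed only | Major | Major | Minor unless the patient dies |
| Unstable spine, neither | Major | No row | Not major unless the patient dies |
| Diaphragm or major pelvic fracture, neither | Insignificant | Minor | Not major unless the patient dies |

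The first three rows are conflicts between major and a lower class. The fourth is a gap in Table 1. The fifth affects only the secondary outcome (major or minor injury).

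The Delphi Results section agrees with the general rule that aortic injuries are major without intervention. Its list of observed minor injuries then includes vascular injuries that do involve the aorta. That is probably a dropped negative. I do not count it as a further conflict, but it needs correcting.

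**Step 2: the plan's figures.** The sample size section plans for 317 major injuries at 5% prevalence: 317 / 0.05 = 6,340 per phase, and 2 × 6,340 = 12,680 in total. Both products reproduce. The 317 does not follow from the printed formula. With X = N the formula reduces to P_L = 0.025^(1/N), which reaches 0.98 at N = 183 and equals 0.9884 at N = 317. That is a separate matter. Below, 317 is used only as the planned number of major injuries.

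**Step 3: how close the verdict is.** Validation of the A/P CT decision instruments requires lower confidence limits above 98%. Only the sensitivity criterion is examined here. With k misses, X = N − k, and the article's formula is P_L = X / (X + (k + 1) · F), with F at 0.025 on 2(k + 1) and 2X degrees of freedom.

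| Misses among 317 | Lower limit | Above 98%? |
|---|---|---|
| 0 | 98.84% | Yes |
| 1 | 98.26% | Yes |
| 2 | 97.74% | No |

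**Step 4: moving one rule-negative patient into major.**

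- From 0 misses in 316 (98.84%) to 1 in 317 (98.26%): still passes.
- From 1 miss in 316 (98.25%) to 2 in 317 (97.74%): pass becomes fail.
- From 2 misses in 316 (97.73%): already failing.

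So one patient reverses the verdict only from a starting point of exactly one miss.

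**Step 5: effect on enrolment, by assumption only.** No frequency is given for the disputed injuries. Suppose the 5% refers to the wider rule and a narrower rule drops a share q of major injuries. Then 317 events need 317 / (0.05 × (1 − q)) patients per phase: 6,405 at q = 1% and 7,045 at q = 10%, against 6,340.

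**The case against.** The strongest reply is that Table 1 is the definition and the rest is shorthand. The Methods text ends by pointing to Table 1, the Phase 1 parentheses read as a gloss, and Table 2 carries the same injury types, lists interventions and gives the aorta and unstable spine their own rows. Ambiguous reports are to be settled blind to clinical variables. The disputed categories may be rare.

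Part of this stands. The Table 2 footnote is looser than Table 1 but does not contradict any row. Four stronger readings should be resisted:

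- **Death.** A reader might infer that death is a competing criterion because Table 1 omits it. Outcome ascertainment counts death under the need for intervention, which largely reconciles the two.
- **Stable spine injuries under observation.** The general rule's wording appears to exclude all spine injuries from minor. But no statement calls a stable injury without intervention major, and Table 1 and the Delphi Results both call it minor.
- **Diaphragm and major pelvic fractures.** Their conflict is between minor and insignificant and does not reach the primary outcome.
- **The one-patient flip.** A reader might infer that any single disputed patient overturns validation. From zero misses, which is the planning assumption, it does not.

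The shorthand reply does not remove the core. The general rule says any aortic injury, and the Delphi conclusions repeat it, while Table 1 says otherwise for one class of aortic injury. The Phase 1 scale departs from both for observed injuries. No sentence gives precedence to any of them.

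**Conclusion.** The point holds for aortic injuries and for unstable or neurologically compromised spine injuries managed without intervention. There are two direct conflicts over major status and one missing row in Table 1. A lesser inconsistency affects the secondary outcome, and the form's footnote is vague. A fuller protocol or analysis plan could choose among the statements but could not make them all true.

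The number of patients affected cannot be computed from the article. The consequence for validation is conditional: at 317 major injuries the sensitivity criterion passes with one miss and fails with two, so a reclassified patient matters to the verdict only if that patient has none of the rule's criteria and exactly one other major injury has been missed. This rests on the article's exact two-sided 95% limit and on 317 being reached. The correction is still needed, because the primary reference standard should not depend on which section a coder reads.

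**What to change.** Reconcile the aortic, unstable-spine, diaphragm and major pelvic fracture entries in the outcome-definition text, Table 1, the Phase 1 scale and the Delphi Results and Conclusions against the recorded panel votes. The Delphi Methods already give the majority and tie rules. This review does not say which class is clinically right.

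Then:

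1. Declare the reconciled Table 1 the single governing definition for both phases.
2. Add a row for unstable-spine injuries needing neither observation nor intervention, and a note that death counts as described under Outcome ascertainment.
3. Replace the Phase 1 parentheses and the Table 2 footnote definitions with a reference to Table 1.
4. Have the form record injury type, intervention, observation and death, so that the class follows from Table 1.

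The cost is protocol and form wording plus one small data item. Table 2 has no field for observation status, and procedural records need not show it, so that field must be added and defined.

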**Insignificant injuries**
Bladder or ureteral injuries that do not need intervention or observation
Bowel injuries that do not need intervention or observation
Gynecological injuries that do not need intervention or observation
Hepatobiliary injuries that do not need intervention or observation
Hip fractures that do not need intervention or observation
Male genital injuries that do not need intervention or observation
Pancreatic injuries that do not need intervention or observation
Pelvic fractures (minor) that do not need intervention or observation
Renal injuries that do not need intervention or observation
Retroperitoneal injuries that do not need intervention or observation
Spinal injuries (stable with no neurological compromise) that do not need intervention or observation
Splenic injuries that do not need intervention or observation
Vascular injuries (pelvic vessels) that do not need intervention or observation
Vascular injuries (other vessels) that do not need intervention or observation

### Core methods

Our basic approach involves collecting assessments on the presence or absence of specific individual candidate criteria, as well as a definitive outcome assessment (presence or absence of A/P injuries) for individual patients with blunt trauma in a large cohort. We will examine different combinations of these criteria to identify a subset that predicts the presence of injury with high sensitivity, while simultaneously exhibiting the highest possible specificity. Our proposed rule will consist of the criteria identified by this process, and risk designation will be based on the presence or absence of the individual criterion, with “low-risk” categorization assigned to individuals who exhibit none of the criteria, and “not low-risk” categorization assigned to those who exhibit one or more of the criteria.

The process used to construct our decision instrument has the potential to create a rule that exhibits superb performance for patients in our derivation cohort, but much lower performance when applied to a new patient cohort. To address this concern, we will conduct a validation study that will evaluate our proposed rule on a new cohort of patients with blunt trauma to determine whether it retains adequate sensitivity to justify clinical application. The potential for decreased A/P CT imaging will be reflected in the specificity observed in the validation phase. The study, along with a condensed summary and list of participating centers, is registered in ClinicalTrials.gov as NCT04937868.

This study has been reviewed and approved by the UCLA Institutional Review Board (UCLA IRB). The study has been granted a waiver of informed consent as it does not alter the care and poses no harm to enrolled patients, and would be impossible to conduct without the waiver.

### Study sites and subjects

This prospective cohort study will be conducted at four Level 1 Trauma Centers, with wide variations in geographic location and patient populations. Including institutions from different environments (urban suburban, rural) enables us to increase the external validity of the instrument and is also necessary to assemble the large cohort of patients needed to obtain high levels of precision, small confidence intervals, and robust measures of sensitivity and negative predictive value that are needed to justify clinical application [8, 9, 11, 12, 16–21, 39, 40].

We will enroll patients using a prospective convenience sample of consecutive patients presenting to the ED between 0700–2300 (the times during which research assistants will be available). We will review ED logs and identify patients who are not enrolled, and we will compare the age, sex and injury severity scores of the enrolled and un-enrolled populations. We will adhere to the Standards for the Reporting of Diagnostic accuracy studies (STARD) guidelines for diagnostic accuracy studies and include a STARD flow diagram [41].

### Inclusion/Exclusion criteria

The study will be observational by design and will not alter the care or management of blunt trauma patients. Medical management will be determined by treating physicians using current standards of care.

To reduce the potential for bias, the study will seek to enroll all victims of blunt injury who undergo A/P CT imaging as part of their ED trauma evaluation. This may include adult patients of all ages, including the elderly, any and all races, both sexes, women who are pregnant or have childbearing capacity, and any other representative demographic or social groups that may present among patients with blunt injuries. An individual will become eligible for the study when the treating physician determines that A/P CT imaging is needed as part of their trauma evaluation. This eligibility criterion aligns with our goal to develop instruments that will be used to safely decrease CT imaging–the fact that clinicians have already decided to order imaging in enrolled patients *en face* supports the notion that our instruments may only serve to decrease CT ordering.

There will be no exclusion criteria. However, while the study will seek to enroll all patients with blunt injury who undergo A/P CT imaging, treating physicians will be able to waive data collection and immediately obtain imaging on any patient they feel is unstable or in whom they cannot complete their study evaluation prior to imaging. These patients will be designated as “unstable,” with stability being an implicit criterion of the rule. Physicians will be requested to complete data entry for these patients at their earliest opportunity, ideally before imaging results are known. This process will not threaten the study validity, however, because instability will be an *a priori* criterion, while blood pressure and heart rate parameters consistent with instability are, themselves, candidate criteria and may become part of the final decision instrument.

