## Objectives

### General design

In this prospective, cohort, multi-center study we seek to develop an imaging decision tool that will enable clinicians to identify patients with blunt trauma who are at “very low-risk” for clinically significant A/P injuries. Implementation of the decision tool will require clinicians to assess the presence or absence of specific clinical findings. Patients with a full assessment of all criteria and who exhibit none of the clinical findings will be designated as “very low-risk”. Patients who exhibit one or more of the clinical findings, as well as those for whom a complete assessment of criteria cannot be completed, will be designated as “not low-risk.” Patients who are designated as very low-risk will have negligible potential to harbor significant A/P injuries, will receive no benefit from A/P CT imaging, and will therefore be safe to exclude from A/P CT imaging. All other patients remain candidates for imaging. It is worth noting that while our project focuses on developing a rule for combined A/P CT imaging, the rule will also be suitable for evaluating patients for isolated abdominal or isolated pelvic imaging. This is a reflection of the fact that patients who are designated as low risk by our instrument will have negligible risk of either abdominal or pelvic injury, and can safely be excluded from abdominal-pelvic imaging, isolated abdominal imaging, or isolated pelvic imaging.

Classification by an optimal decision instrument will reflect a balance between the risk of imaging (malignant transformation from exposure to ionizing radiation), the costs of CT, and the risks of not imaging (potential harm from unrecognized significant injuries). Because the rate of lethal malignant transformation is low, the decision tool must exhibit high sensitivity to ensure that the missed injury rate is very low, and that virtually all patients with significant injuries are designated as “not low risk.”

To be clinically useful, the decision tool must also assign low-risk classification to as many uninjured patients as possible. This is equivalent to requiring the tool to produce as few false positive results as possible, or equivalently, exhibit high specificity. The proportion of patients who can safely be spared imaging is directly related to the instrument’s specificity, so the development process will focus on identifying a tool with the highest possible specificity.

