### Phase 2: Validation of low-risk decision instruments for A/P CT imaging

At the completion of the derivation phase, we will begin enrolling patients into a validation study to assess, and attempt to validate, the test characteristics of our newly developed decision instruments. We will record the presence or absence of the individual criteria of the new decision tool(s), and we will combine these assessments with results of A/P CT imaging and clinical course to form our validation data set. We will evaluate criteria in the validation phase using methodology similar to that used in the derivation phase, although two aspects of assessment will change between the two phases. The first change reflects the reduced number of number of criteria assessments that need to be completed on each patient in the validation phase, as clinicians will only need to assess criteria included in the derived rule(s). A second important difference between the two phases involves the handling of un-assessed criteria. In the validation phase, and in the ultimate application of the rule, each criterion will be considered positive (abnormal) unless it can be assessed and found to be normal. Thus, variables that cannot be measured in an individual patient (such as pain in an unconscious individual) will be documented as “unable to assess” and treated analytically as positive. This assures that low-risk status, and exclusion from imaging, is based on actual observations of normal findings, and prevents low-risk assignment on the basis of inadequate or incomplete assessment.

Clinical outcomes and injury assessments in the validation phase will be identical to those completed in the derivation phase.

We will assign risk status to each patient based on the criteria assessments, and use these risk assessments in combination with outcome assignments to calculate point measures and 95% confidence intervals for sensitivity, negative predictive value, specificity, and estimated potential reductions in imaging that might be achieved by implementation of each of the rules (both minor and major injuries).

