#### Results

The physicians exhibited substantial inter-rater agreement for the following criteria: abdominal pain or tenderness (π = 0.64), flank pain or tenderness (π = 0.43), pelvic pain or tenderness (π = 0.41), hip or iliac pain or tenderness (π = 0.49), midline lumbar spine or sacral pain (π = 0.47), abnormal alertness (π = 0.48), evidence of intoxication (π = 0.68), distracting painful injury (π = 0.43), and hypotension (π = 0.63).

The physicians exhibited moderate or poor inter-rater agreement (π < 0.40) for abdominal distention, and abdominal or pelvic bruising or abrasion, tachycardia, unstable vital signs, and low or falling hemoglobin or hematocrit. The clinicians also exhibited poor inter-rater agreement on evidence of genital-urinary trauma (π = 0.23), but the exclusion of this criterion is mitigated by the fact that there were no patients who sustained significant genital-urinary trauma among our inter-rater assessment cohort.

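### The unstable label also covers patients whose study form was merely unfinished, and allows criteria entry after CT results, so the claim that validity is not threatened is unsupported

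*Protocol article*

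**What the plan says.** All of this is in the protocol article.

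- **Who may be waived** (Inclusion/Exclusion criteria): data collection may be waived for any patient felt to be "unstable or in whom they cannot complete their study evaluation prior to imaging". Both kinds of patient receive the label unstable, "with stability being an implicit criterion of the rule".
- **When their criteria are entered** (same section): "Physicians will be requested to complete data entry for these patients at their earliest opportunity, ideally before imaging results are known". Entry before the result is an ideal, not a requirement.
- **What is claimed** (same section): "This process will not threaten the study validity, however, because instability will be an" a priori criterion. A second reason follows: blood pressure and heart rate parameters are themselves candidate criteria.
- **Incomplete assessment** (General design): patients with a positive finding, "as well as those for whom a complete assessment of criteria cannot be completed, will be designated as" not low-risk. In Phase 2, "each criterion will be considered positive (abnormal) unless it can be assessed and found to be normal". In Phase 1 the convention is reversed and un-assessed items count as negative.
- **What decides validation** (Validation of the A/P CT decision instruments): the lower confidence limits of sensitivity and NPV must exceed 98%. A true positive is an injured patient with at least one of the variables. The implicit stability criterion is not mentioned there.
- **Reliability of the vital-sign criteria** (Preliminary work, inter-rater Results): agreement was below 0.40 for criteria including "tachycardia, unstable vital signs, and low or falling hemoglobin or hematocrit". Hypotension reached 0.63. Phase 1 sets 0.40 as the threshold for inclusion.

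**The concern.** The label joins two different groups. Truly unstable patients, or patients who cannot be assessed, would be imaged under the rule in practice, so a positive classification describes the rule correctly. A stable, assessable patient whose study form was not finished in time is positive only because of how the study was run. In later use the clinician would assess that patient, and the rule might miss the injury. In the validation count it cannot be missed.

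Entry after the CT result is a second route. A clinician who knows there is an injury may be readier to record tenderness or a distracting injury. The only blinding described (Outcome ascertainment) covers investigators classifying ambiguous reports, not the clinician entering criteria. Data analysis removes only cases lacking radiographic reports or intervention outcomes, so late entries stay in.

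At stake is the sensitivity bound on which the instrument is declared validated and, in derivation, the choice of criteria.

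**Working it through.** **1. The plan's own figure.** With no misses, the stated lower limit N/(N + F) at α/2 = 0.025 equals 0.025^(1/N). Setting this to 0.98 gives N = ln 0.025 / ln 0.98 = 182.6, so 183, not the stated 317. (The same formula does give the 368 of the work-up bias section.) That discrepancy is a separate matter. Here 317 is taken as the planned number of injured patients; 317/0.05 = 6,340 per phase agrees with the text.

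**2. What passes with 317 injured.** Exact two-sided 95% lower limits are 98.84% with 0 misses, 98.26% with 1 and 97.74% with 2. Validation on sensitivity therefore allows at most one miss.

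**3. Two readings of the true-positive definition.**
- *The implicit criterion counts.* Every waived injured patient is a true positive by label. Late entry then cannot change that patient's validation result.
- *It does not count.* The criteria as entered, possibly with the CT result known, decide true positive versus false negative. No figure in the document allows this to be sized.

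In validation these are alternatives and must not be added. In derivation, un-assessed items count as negative, so late entry can turn a negative into a positive selectively among the injured and steer which criteria are chosen.

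**4. Size under the first reading.** Let w be the share of the 317 injured who are positive by label alone (an assumption; the document gives none) and s the sensitivity in the n = 317(1 − w) assessed. Sensitivity as classified is w + (1 − w)s. The chance of at most one miss is s^n + n(1 − s)s^(n−1). With s = 0.98:

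| w | n | Sensitivity as classified | Chance of meeting the bound |
|---|---|---|---|
| 0% | 317 | 98.0% | 0.0017 + 0.0107 = 1.2% |
| 10% | 285 | 98.2% | 2.2% |
| 20% | 254 | 98.4% | 0.0059 + 0.0306 = 3.7% |
| 30% | 222 | 98.6% | 0.0113 + 0.0511 = 6.2% |
| 50% | 158 | 99.0% | 17.4% |

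Only the part of w due to unfinished forms is inflation. The part due to true instability belongs to the rule.

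**5. When the pass/fail result could change.** On assessed patients alone, one miss still passes with at least 277 patients, that is w up to 1 − 277/317 = 12.6%. Zero misses still pass with at least 183, that is w up to 1 − 183/317 = 42%.

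**6. Does the NPV bound compensate?** Waived patients are never low-risk, so NPV is not diluted. But at the plan's 10% rule-negative share (634 of 6,340), NPV still passes with 5 misses (lower limit 98.17%), whereas sensitivity allows 1. Sensitivity is the binding guard, and it is the one affected.

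**7. The stated safeguards.** The first, instability as an a priori criterion, holds for truly unstable patients and does not depend on inter-rater agreement. It says nothing about a stable patient with an unfinished form. The second is half weakened: tachycardia and unstable vital signs fell below the plan's own threshold, while hypotension passed. Neither addresses entry after the result.

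**The case against.** The strongest reply is that the rule is defined this way. An incomplete assessment means not low-risk, in validation and in use, so waived patients are correctly positive. That stands for truly unstable and unassessable patients. It does not cover patients who could have been assessed but whose form was late.

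Three stronger readings are tempting and not supported:

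- *Automatic positivity and late entry together inflate validation sensitivity.* They are alternatives, as step 3 shows.
- *The 3.7% and 6.2% breach a nominal 2.5% error rate.* The 2.5% belongs to sensitivity over all patients as classified, which at those shares is 98.4% and 98.6%. How much of that gain is legitimate depends on the split between the waiver reasons, which is unknown.
- *The primary analysis should be restricted to criteria recorded before the CT result.* That changes the quantity estimated, drops the sickest patients against the stated aim of enrolling everyone imaged, and is costly. At true sensitivity 99.5% with 20% waived, the chance of meeting the bound falls from 64% (at most 1 miss in 254) to 28% (0 misses in 254); at 30% waived, from 70% to 33%.

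It is also fair to say that waived uninjured patients become false positives and lower specificity, so the effect does not all favour the rule. Time stamps may exist in the data form, which is not shown; the text says date and time are collected. The point therefore rests on what the article states, the merged label and the assurance about validity, and not on an absent data field.

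**Conclusion.** The point holds in a limited form and should be corrected. The label mixes true instability with unfinished study forms, criteria may be entered with the CT result known, and the true-positive definition does not say whether the label counts. Under one reading, sensitivity is raised by stable patients who cannot be missed. Under the other, unblinded entries can decide the classification. The assurance that validity is not threatened does not follow from the reasons given.

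Under the first reading the direction is certain for patients waived only because a form was unfinished: they can raise but not lower validation sensitivity. The size is not known. The range of 1.2% to 6.2% for waived shares of 0% to 30% assumes 317 injured, 98.0% sensitivity in assessed patients and an invented share. Below about 12.6% waived, a result with 0 or 1 miss would pass either way.

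**What to change.** 1. Record separately whether data collection was waived for instability or because the evaluation was incomplete.
2. Time-stamp criteria entry against availability of the CT result.
3. In the validation section, state whether the implicit instability criterion counts as a positive.
4. Do not use criteria entered after the CT result as observed findings, in either phase.
5. Keep all patients as the primary analysis. Prespecify sensitivity, NPV and specificity also without patients waived for incomplete evaluation and without late entries, and report those patients separately.
6. Replace the statement that validity is not threatened with a description of the two groups and of this analysis.

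The cost is one data field, a time stamp and a wider interval in the restricted analysis. For example, with 254 assessed the lower limit is 98.56% with no misses and 97.83% with one.
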